#### 2.5.2. Disability Index

The level of functional disability of participants resulting from LBP will be measured using the Revised Oswestry Low Back Pain Disability Index (ODI). The scale is one of the most reliable and effective outcome measures for evaluating patients with LBP [38]. The scale comprises 10 items questioning pain intensity related to activities of daily living. Each item provides six statements describing an increase in the level of severity of a particular activity, which is scored from 0–5 points. The total is calculated by multiplying the sum of the scores by 2, giving a range of 0 to 100 percent; a higher score reflects a higher disability [39].

#### 2.5.3. Perceived Musculoskeletal Discomfort during Prolonged Sitting

Perceived musculoskeletal discomfort during prolonged sitting will be measured using the Borg CR-10 scale during 1 h of sitting [40]. The body regions (i.e., the neck, shoulder, elbow, wrist, upper back, low back, buttocks, hip/thigh, knee, and ankle) will be defined according to a body chart from a modified Nordic questionnaire [41]. Participants will indicate which parts of their body experienced musculoskeletal discomfort and how much discomfort was felt (on a scale of 0–10; 0 denotes no discomfort and 10 denotes extreme discomfort).

#### 2.5.4. The Global Perceived Effect

The global perceived improvement will be assessed using The Global Perceived Effect Scale (GPE) [42,43]. It is a 7-point numerical scale (1–7). The participants will be asked: “Since the start of treatment, my current overall status is”: 1 = completely recovered, 2 = much improved, 3 = slightly improved, 4 = not changed, 5 = slightly worsened, 6 = much worsened and 7 = worse than ever. These ratings will be dichotomized into “improved” (GPE scores 1–2) and “not improved” (GPE scores 3 to 7) [44].

### 2.6. Secondary Outcome Measures

#### Post-Intervention Questionnaire

The postIQ will be focused on the opinions of the participants in relation to the active break program. The questions, among others, will be focused on perceived health, on the perceived improvement in knowledge of health-related topics, on the musculoskeletal symptoms during the program, on the usefulness of the content learned during the program, on the capability of incorporating the content learned during the program in daily living and on the exercises that were practiced at home. The items will be presented in the form of statements to which students will be asked to respond using a 1–5 Likert scale (“strongly agree”, “agree”, “not sure”, “disagree”, and “strongly disagree”).

### 2.7. Intervention Protocol

The intervention will be divided into the following two groups:

Group 1 (AB-group): participants will receive recommendations to take an active break with proposed lumbar and hip extension and hyperextension exercises for every 30 min of sitting.

Group 2 (C-group): participants will receive self-care recommendations and will be encouraged to remain active, performing their regular baseline activities.

### 2.8. Active Break Program

The experimental group will receive recommendations to take an active break every 30 min of sitting for 12 weeks. In the experimental intervention, the active break program will include lumbar and hip extension exercises and will be based on self-education with an explanation of the importance of regular training. The participants will receive a booklet with photographed and described exercises. The education will be carried out by an experienced physiotherapist.

The habit of doing exercises during an active break will be formed gradually (Table 2). In the first month, participants will be instructed to perform the proposed exercises in a standing position with lumbar and hip extension every 30 mins or whenever musculoskeletal discomfort occurs. In the second month, the complexity of the active break exercises will be increased by progressing to spine hyperextension exercise. In the third month, participants will be instructed to also perform spine hyperextension exercise in a sitting position. The number of repetitions depends on the needs of the participants.

### 2.9. Control Group

Participants assigned to the control group will receive an educational self-care book containing information on LBP, the anatomy of the spine and its relationship to the muscular chain, care during daily life activities and the importance of regular physical exercises. The control group will perform their regular baseline activities and will be advised to not alter their current behavior routine. Participants will be asked not to look for other treatments outside the trial during the intervention period.

Participants assigned to the control group will be offered the option of joining the exercise program with an active break after the final assessment has been completed.

### 2.10. Procedure

All 1st- and 2nd-year students of Physical Education will be informed of the research procedures, and those that are interested will be provided with a brief introduction to the selection process. One researcher from the university will conduct a pre-screening self-administered questionnaire (on paper) during classes with students. The pre-screening will address basic demographic data, the frequency of LBP, and the specific inclusion and exclusion criteria for this study. LBP will be assessed using the following question: “Have you experienced low back pain for the last 3 months?”. The answer options were: “no”, and “yes”. “Yes” was considered to denote the presence of LBP. A blinded assessor will evaluate the eligibility criteria. Participants who meet the inclusion criteria will be invited to the main study.

Before the baseline assessment, written consent will be obtained from the participants. At the baseline assessment session, participants will be requested to complete the VAS, Revised ODI, and Borg-10 scale. The baseline assessment will be conducted before the random distribution of the participants into the groups. After completion of the baseline assessment, participants will be randomly assigned into one of the two groups (AB-group or C-group), and simultaneous implementation of the two programs will commence. To improve adherence, participants from AB-group will send daily reports about hours in sitting positions and the number of active breaks via the Messenger^®^ application. Participants from C-group will be asked not to look for other treatments outside the trial during the interventions.

The assessment of the outcomes will be collected at baseline and immediately after the 12-week intervention.

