#### 2.1.1. Inclusion Criteria

Participants will be recruited according to the inclusion criteria: female and male; age between 18 and 25 years; experiencing non-specific LBP (defined as pain and discomfort localized below the costal margin and above the inferior gluteal folds), without radiation to legs; not using medication for low back pain in the last 3 months; not having a surgical history due to spinal problems; not having radiculopathy or other injuries such as fractures, stenosis or tumors in the spine; lack of any treatment related to the low back within the last 6 months.

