#### 2.1.2. Exclusion Criteria

Participants will be excluded from this study if they experience a level of low back pain of at least 7 on the 0–10 Visual Analogue Scale (VAS) scale (where 0 and 10 are “no pain” and “most severe pain I can imagine”, respectively); spinal pathology (e.g., tumor, infection, fracture, inflammatory disease); pregnancy; nerve root compromise; previous spinal surgery; major surgery scheduled during treatment or follow-up period; disc herniation; leg length discrepancy; pelvic asymmetry; and presence of any contraindication to exercise. In order to achieve homogeneity in terms of physical activity, professional athletes will be also considered ineligible.

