### 2.3. Pre-Intervention Questionnaire

The survey contained questions regarding:-gender,-age,-current physical activity (sports discipline, number of training days and hours per week),-illnesses, injuries, surgical history due to spinal problems, treatment related to LBP, diagnosed defects in body posture,-experience of LBP within the last three months. Individuals who respond positively (“yes”) to the question “Have you experienced low back pain for the last three months?” will then answer the question in the frequency of experiencing LBP (rarely, few times per week, often, or constantly) and the types of situations in which LBP occurred or increased.

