### 2.5. Primary Outcome Measures

#### 2.5.1. Pain Intensity

Average pain intensity will be assessed with the VAS. VAS is a validated, objective and unidimensional measure of pain [36]. Participants will be asked to rate their maximal pain intensity from the last 3 months on a 10 cm line. The centimeters will be marked by the participants and will be measured and classified according to the following key: 0—no pain, 1–3—mild pain, 4–6—moderate pain and 7–10—severe pain [37].

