### 2.11. Study Procedures

#### 2.11.1. Sample Size

The sample size was determined using the software G*Power 3.1, which used Factorial ANOVA with assumption of a medium-sized effect (d = 0.50) at a significance level of 0.05 and statistical power of 0.85. Therefore, the required sample size for this study will be 50 participants randomly assigned in two different groups. The sample will be increased by 20% to compensate for possible dropouts, leading to 32 individuals in each group (overall sample = 64 participants).

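### The request not to seek outside treatment during the 12 weeks is written for the control group only; address it to both arms

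*Protocol article*

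**What the plan says.** The request appears twice in the protocol article. Section 2.10 (Procedure) names the arm: "Participants from C-group will be asked not to look for other treatments outside the trial during the interventions". Section 2.9 (Control Group) has: "Participants will be asked not to look for other treatments outside the trial during the intervention period". There the subject is simply the participants, but the sentence stands among others that describe the control arm.

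The sentence just before the request in Section 2.10 gives the other arm a different task: "participants from AB-group will send daily reports about hours in sitting positions and the number of active breaks". Sections 2.7 and 2.8, Table 2 and Section 3 (adherence) say nothing about other treatment for the active break group.

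Both arms do share an entry criterion in Section 2.1.1: "lack of any treatment related to the low back within the last 6 months". The same section bars recent medication for low back pain (last 3 months). Both criteria look back from entry and do not cover the 12 weeks of intervention.

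**The concern.** A randomised comparison should differ between arms only in the intervention under test. Asking one arm alone to avoid other treatment adds a second difference, and the design has no need of it. If the request changes behaviour, the arms may end up with different amounts of outside care for the back.

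The four outcomes defined in Section 2.5 (pain on the VAS, the Oswestry index, Borg discomfort and the Global Perceived Effect) all rest on what participants report, so effective outside care could move any of them. The intention-to-treat comparison would then estimate the active break programme together with any imbalance in co-treatment, and could not separate the two. At stake is a clean interpretation of the between-arm difference. The request may well be meant to keep the comparator stable, but that aim does not require leaving out the other arm.

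**Working it through.** **Step 1: the text, side by side.**

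| Place | Who is addressed | Outside treatment during the 12 weeks |
|---|---|---|
| 2.1.1, 2.1.2 Eligibility | everyone | no rule; the treatment criteria concern the time before entry |
| 2.7 Intervention Protocol | both arms, separately | nothing for either |
| 2.8 Active Break Program, Table 2 | active break group | nothing |
| 2.9 Control Group | participants, under the control heading | asked not to seek it |
| 2.10 Procedure | control group by name | asked not to seek it |
| 3 Adherence | participants | adherence and adverse events only |

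The request is stated twice. Once it is explicitly for controls, and once it sits in the control section. It is never directed at the active break group or expressly at both arms. So the article states a rule and attaches it to one arm, which is more than leaving out a detail.

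**Step 2: a rough size.** The plan gives no figure for outside treatment, so there is none to reproduce. The inputs are:

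- n per arm: 32, from Section 2.11.1 ("leading to 32 individuals in each group"), or 25 before the dropout allowance (50/2).
- Yardstick: the planning effect d = 0.50 in the same section.
- k, the excess users of outside treatment in one arm: 1 to 3 (assumed).
- e, the effect per user: 0.2 to 0.5 SD (assumed).

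Formulas: bias = (k/n) × e, and standard error of the difference in means = √(2/n), both in SD units.

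| | n = 32 per arm | n = 25 per arm |
|---|---|---|
| Low | 1/32 × 0.2 = 0.006 SD | 1/25 × 0.2 = 0.008 SD |
| High | 3/32 × 0.5 = 0.047 SD | 3/25 × 0.5 = 0.060 SD |
| As a share of d = 0.50 | 1% to 9% | 2% to 12% |
| Standard error | √(2/32) = 0.25 SD | √(2/25) = 0.283 SD |
| High ÷ standard error | 0.047/0.25 = 0.19 | 0.060/0.283 = 0.21 |

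**Step 3: what a noticeable bias would take.** For 0.1 SD with 32 per arm, k = (0.1/e) × 32. With e = 0.5 this is 6.4, so 7 users; with e = 0.2 it is 16. An excess of 7 to 16 users out of 32 looks unlikely. Recent low-back treatment is barred at entry, and Section 2.1.2 also excludes people "if they experience a level of low back pain of at least 7" on the VAS, so low use is plausible in both arms.

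**Step 4: the sign.** It depends on which arm has more users, and the article gives no information on that.

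**The case against.** The best case against the point is that the active break side rests on silence in a condensed article. Rules on concomitant care and the exact wording given to participants commonly sit in a full protocol or information sheet, which is not shown. The sentence in Section 2.9 is also less one-sided than its heading suggests: its neighbours name the control group and it does not. Further, the request has a function in the control arm. Controls are to keep their routine, receive only a book and are offered the programme after the final assessment, so they may have more reason to look for care. Restraining them could reduce differential co-treatment.

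Much of this stands, and it limits the point. Four stronger readings that a reader might infer are not supported:

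- *The active break group is allowed other treatment.* No sentence grants this; silence is not permission.
- *The bias favours the active break group.* The argument just given about controls' motives cuts the other way, and nothing in the article fixes the sign.
- *The three-month VAS recall makes the trial especially vulnerable.* Section 2.5.1 says: "Participants will be asked to rate their maximal pain intensity from the last 3 months on a 10 cm line". That window does span about the whole intervention. But treatment sought because of a painful episode comes after the peak has occurred, and can lower the maximum only by preventing a later, higher one.
- *The lack of a week-12 question on outside treatment is a defect.* Such data-collection detail may be left to the full protocol, and the article describes the Post-Intervention Questionnaire only in part.

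The objection does not remove the explicit wording of Section 2.10, which gives this instruction to the control group by name directly after a different one for the other arm. Nor does the purpose of protecting the comparator give a reason to leave the active break group out.

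**Conclusion.** The point holds as a minor one. As published, the request is arm-specific. This is an avoidable difference between arms that could produce unequal co-treatment. The textual part is firm. The size is not: under the assumed inputs it runs from 0.006 to 0.060 SD, at most 12% of the planning effect and about one-fifth of a standard error, with unknown sign. A bias of that order would be unlikely to change the trial's conclusion. The case for acting rests on the clear wording and the very low cost of correcting it.

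**What to change.** In Sections 2.8 to 2.10, give both arms the identical request not to seek other low-back treatment during the intervention period. This takes one sentence in the participant instructions.

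Optionally, ask both arms at week 12 whether they used outside treatment or analgesics for the back, and report the answers by arm. The Pre-Intervention Questionnaire in Section 2.3 already covers "treatment related to LBP, diagnosed defects in body posture", so its treatment item could be reused. Do not adjust the outcome comparison for the answers, because co-treatment arises after randomisation.

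The cost is the added sentence and, if the option is taken, one more question, which is a negligible burden on participants. Sample size, randomisation and analysis stay as they are.

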### 2.11. Study Procedures

#### 2.11.1. Sample Size

The sample size was determined using the software G*Power 3.1, which used Factorial ANOVA with assumption of a medium-sized effect (d = 0.50) at a significance level of 0.05 and statistical power of 0.85. Therefore, the required sample size for this study will be 50 participants randomly assigned in two different groups. The sample will be increased by 20% to compensate for possible dropouts, leading to 32 individuals in each group (overall sample = 64 participants).

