### 3.1. Statistical Analysis

The data will be analyzed using Statistica 14.0.0.15 program (TIBCO Software Inc., Palo Alto, CA, USA, 2020). The parameters will be described using basic descriptive statistical measurements, i.e., the percentage for qualitative variables, and the mean and standard deviation for quantitative variables. For variables that do not meet the criteria of normality of distribution, data will be presented as medians and quartile ranges. The normality of the distributions of the quantitative variables under study will be tested using the Shapiro–Wilk test. To verify the homogeneity of variances, Lavene’s test will be conducted. The chi-square test will be used for categorical variables. Descriptive statistics will be calculated separately for all groups (active break vs. control). The Student’s *t*-test (if data meet the criteria of normality of distribution) and the Mann–Whitney U test (if data do not meet the criteria of normality of distribution) will be used to compare parameter values between groups (active break vs. control). The Wilcoxon signed rank test will be used to examine the differences in parameters (VAS, ODI and discomfort) before and after the intervention. Intention-to-treat analysis will include all randomized patients. The significance level will be set at *p* < 0.05.

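### The stated 85% power for d = 0.50 with 50 participants does not follow: the planned two-group comparison has about 41% power with 50 and 50% with all 64

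*Protocol article*

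**What the plan says.** Protocol article, section 2.11.1 (Sample Size), states that G*Power 3.1 was used with "Factorial ANOVA with assumption of a medium-sized effect (d = 0.50) at a significance level of 0.05 and statistical power of 0.85". From this it concludes that "the required sample size for this study will be 50 participants randomly assigned in two different groups". It then adds a dropout allowance: "The sample will be increased by 20% to compensate for possible dropouts, leading to 32 individuals in each group (overall sample = 64 participants").

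The section does not give the numerator degrees of freedom, the number of cells, a correlation between repeated measurements, or the outcome to which the effect size applies. Section 2.4 lists five primary outcomes.

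Section 3.1 (Statistical Analysis) contains no ANOVA. It says that Student's t-test or, if normality fails, the Mann-Whitney U test "will be used to compare parameter values between groups (active break vs. control"). Change from before to after the intervention is tested with the Wilcoxon signed rank test.

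**The concern.** Effect size, significance level, power, number of groups and sample size are all printed, so the calculation can be checked, and 25 per arm is far too few for 85% power at a half standard deviation difference. Two further features suggest how the figure went wrong. G*Power's factorial ANOVA takes Cohen's f, not d, so a value of 0.50 may have been entered on the wrong scale. The method used for sizing is also not the method planned for the analysis.

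This calculation is the only justification given for the size of the trial. If it is wrong, the trial claims a power that it does not have, and a non-significant result would say little about whether a medium-sized benefit exists.

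**Working it through.** **Inputs.** From section 2.11.1: d = 0.50, alpha 0.05, power 0.85, N = 50 (25 per arm), raised to 64 (32 per arm). From section 3.1: two-sample t-test or Mann-Whitney test. Assumptions: two-sided testing (sidedness is not stated; an ANOVA F test corresponds to a two-sided t-test) and an unadjusted comparison.

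**1. Attempt to reproduce N = 50 from the stated inputs.**
- Normal approximation: n per arm = 2(1.960 + 1.036)² / 0.50² = 71.8, so 72.
- Exact noncentral t: power is 0.846 at 72 per arm and 0.851 at 73. The requirement is **73 per arm, 146 in total**.
- Factorial ANOVA: for two equal groups f = d/2 = 0.25. With noncentrality f²N and 1 numerator df, N = 146 again.

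The stated 50 is not reproduced.

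**2. Power at the stated sizes.** The noncentrality parameter is d√(n/2), with 2n − 2 df.

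| n per arm | Noncentrality | Critical t | Power, t-test | Power, Mann-Whitney (approx.) |
|---|---|---|---|---|
| 25 | 0.50 × √12.5 = 1.768 | 2.011 (48 df) | 0.410 | 0.39 |
| 32 | 0.50 × √16 = 2.000 | 1.999 (62 df) | 0.504 | 0.49 |

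The Mann-Whitney column assumes normal data (relative efficiency 0.955). The second row holds only if nobody drops out; with the dropout allowed for in the plan, power returns to about 0.41.

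**3. Effect detectable with 85% power** (same formula solved for d): d = 0.865 with 25 per arm and d = 0.761 with 32 per arm.

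**4. Other routes to 50.**
- One-sided t-test: 59 per arm (118 in total); power 0.54 at 25 per arm and 0.63 at 32.
- 0.50 entered as f, which means d = 1.0: N = 38–39 with 1 numerator df, 47–48 with 2, 54 with 3. None is 50, and a two-group contrast has 1 df.
- Paired t-test, d = 0.50: N = 38.
- Repeated-measures group-by-time interaction, f = 0.25, two time points, noncentrality f²N × 2/(1 − ρ): N = 53 at ρ = 0.3, 38 at ρ = 0.5. At N = 50, power is 0.849 for ρ = 0.33 and 0.854 for ρ = 0.34. So 50 appears only if ρ is about 0.33–0.34.

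In that last model each cell's interaction deviation is f × SD, so the difference in change between groups is 4 × 0.25 = 1.0 SD. A difference in change of 0.5 SD is f = 0.125, for which power at N = 50 is 0.32 (ρ = 0.33) or 0.41 (ρ = 0.5).

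**5. Would baseline adjustment rescue the claim?** None is planned and no correlation is given, so r is assumed. ANCOVA replaces d by d/√(1 − r²).

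| Assumed r | Power for d = 0.50, 25 / 32 per arm | d detectable at 85% power, 25 / 32 per arm |
|---|---|---|
| 0.5 | 0.52 / 0.62 | 0.75 / 0.66 |
| 0.7 | 0.68 / 0.79 | 0.62 / 0.54 |

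**6. Dropout step.** 25/(1 − 0.20) = 31.25, rounded up to 32 per arm. This step is consistent. Applied to the correct figure it gives 73/0.80 = 91.25, so 92 per arm (184 in total).

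**The case against.** The best defence is that the design has two groups and two time points, so the named ANOVA may have been a group-by-time analysis with f = 0.25, the conventional medium value. That does return 50 at a pre-post correlation of about 0.34, and a fuller protocol might hold that correlation. The route the authors took is therefore unknown. The defence does not save the printed claim: the text gives d rather than f, section 3.1 plans no such model, and that f stands for a 1.0 SD difference in change, twice what d = 0.50 would mean.

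It can also be said that 41% and 50% rest on two-sided, unadjusted testing, neither of which is spelled out, and that the comparison of parameter values between groups in section 3.1 could cover change scores. This is fair, and the assumptions should be stated. But one-sided power is 0.54 and 0.63. For change scores, power is 0.41 and 0.50 at an assumed correlation of 0.5, and 0.61 and 0.72 at 0.7. A correlation of 0.8 or more would be needed to approach or pass 85%, and the plan states none.

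Finally, keeping 64 participants is only one remedy; a larger sample or a justified larger target effect are others, and the choice is the sponsor's. Adding ANCOVA would also create a new mismatch unless section 3.1 changed with it. Both points stand, and ANCOVA is therefore only optional in the fix.

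**Conclusion.** The concern holds. On the stated inputs the required sample is 146, not 50, almost three times as many. The comparison planned in section 3.1 has about 41% power for d = 0.50 with 50 analysed and about 50% with all 64, against the 85% claimed. A true medium effect would be missed in about half to three-fifths of such trials.

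These figures assume two-sided 5% testing, equal arms and an unadjusted comparison. One-sided testing, or baseline adjustment with an assumed correlation of 0.5 or 0.7, narrows the gap but does not bring power to 85% at either sample size. The mismatch between the sizing method and the planned analysis is on the page and does not depend on these assumptions. The lack of a named outcome for the calculation is a secondary point. Because the only justification for the trial's size is numerically wrong, it must be corrected.

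**What to change.** Rewrite section 2.11.1 for one named primary outcome and the test in section 3.1, and delete the reference to factorial ANOVA. If the sample stays at 64, suitable wording would be: *With 25 completers per arm, a two-sided 5% t-test has 85% power to detect a standardised difference of about 0.87 and about 41% power for 0.50; if all 32 per arm are analysed, these figures are about 0.76 and 50%.* Add that a non-significant result does not rule out a medium effect.

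Optionally, make ANCOVA on the baseline value the primary comparison. With an assumed r = 0.5 it lowers the detectable effect to d = 0.75 with 25 completers per arm. In that case change section 3.1 as well, and state the correlation as an assumption.

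The cost is a reworded paragraph. No more participants are needed, but the stated power becomes less favourable. If the sponsor wishes to keep 85% power for d = 0.50 with the planned test, the cost is instead 73 completers per arm, or 92 per arm randomised with the 20% allowance.
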